**C4C flow diagram.**

### Study settings

The HIV clinic at San Francisco General Hospital (SFGH), also known as Ward 86, is one of the oldest and largest public HIV clinics in the United States, serving 3,000 low-income patients as part of San Francisco County’s safety-net hospital. Patients at Ward 86 represent multiple urban populations, including the recently incarcerated, substance users, homeless and unstably housed individuals, and those with mental illness. Approximately 12% of clinic patients are women, 25% are African-American and 20% are Hispanic/Latino. Consistent with national guidelines, the clinic standard of care is to offer antiretroviral therapy to all individuals, irrespective of CD4 cell count [28]. The clinic standard of care is also to provide reminder phone calls to patients at least 2 days prior to primary care appointments, however, the consistency of this practice is dependent on staffing levels. Patients are screened for eligibility in the clinic, but baseline, 6, and 12-month study visits take place at a clinical research site in the community. This separate study site minimizes the likelihood that participation in the study influences the key secondary outcome of retention in clinic care.

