#### SMS interactions with participants

Information on pending primary care appointments is downloaded from the hospital electronic medical record and transmitted automatically to a text messaging platform that sends SMS reminders two days prior to HIV primary care appointments. All study participants receive reminders stating, “You have an appointment on Tuesday, June 18th, at 11:30 am with your provider at SFGH, Building 80, 6th floor. Please call XXX-XXX-XXXX to cancel or reschedule”. Participants choose morning or afternoon times during business hours to receive appointment reminders, so that they can call the clinic to reschedule if they are unable to make the appointment.

All participants also receive a monthly text message that reads, “This is your monthly check in from C4C. Thanks for your participation. Please respond C to confirm you received this message”. If participants do not respond to the monthly check-in message, a research assistant calls the participant to ensure that the phone is working and contact information is up to date, unless the participant is in the intervention arm and noted to have responded to an intervention message in the week before or after the check-in message (see *C4C Intervention* below). The monthly check-in message was designed to promote study retention among control arm participants and to track their length of follow-up in the study, as some participants may only have primary care appointments scheduled every three to four months.

Participants are counseled on the potential for bugs and glitches in the SMS system and informed that it is not a method for communicating with study staff or with the clinic. A reply to any study SMS that does not ask for response, including the SMS appointment reminders, results in the message, “Thanks for the feedback. If this is an emergency, please call 911”. At the enrollment visit, a research assistant programs the number from which text messages are sent into the participant’s phone as “C4C Study”.

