### Key secondary outcomes

A three-level ordinal retention variable that incorporates an assessment of *missed visits* as well as *six-month visit constancy*.○ High: Attended all scheduled primary care appointments in both 6-month study periods○ Moderate: Attended at least one scheduled clinic appointment in both 6-month study periods○ Low: Attended no scheduled clinic appointments in at least one 6-month study period*Visit adherence rate*, defined as the number of primary care appointments kept divided by the number of appointments scheduled, excluding cancelled or rescheduled visits.

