#### Follow-up of study participants

Follow-up study visits occur at a community-based research site rather than in the same building as the clinic in order for the study to avoid influencing attendance at clinic visits. Both intervention and control arm participants are asked to complete 6 and 12 month study visits, at which time participants complete a self-administered questionnaire that collects secondary outcomes. If no viral load is resulted or pending in the EMR from the past 28 days then phlebotomy is performed for viral load assessment. Participants receive check-in phone calls at 3 and 9 months to remind them of the upcoming study visit and confirm that the participant’s contact information remains up to date (Figure 2).

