A log-binomial model will also be used to estimate 12-month mean (95% CI) visit adherence rate by arm and the relative rate between arms, adjusted for the stratification factor and correlation among responses per participant. Like the virologic suppression outcome, the ordinal retention in care outcome will be evaluated for each 6-month study period. For each participant, two indicators per period will be calculated: all scheduled primary care appointments were kept (true/false) and some scheduled primary care appointments were kept (true/false). At the end of the trial, the data will be further reduced to two indicators: all scheduled primary care appointments kept in both periods or some scheduled primary care appointments kept in both periods. Trial-level outcomes will be analyzed using an ordinal logistic regression model to estimate threshold-specific mean (95% CI) odds of retention in HIV care by arm and odds ratios between arms, adjusted for the stratification factor and number of scheduled study visits. If model diagnostics indicate that the proportional odds assumption does not hold, each threshold (all kept vs. fewer than all kept; some/all kept vs. none kept) will be modeled via a logistic regression model. A model extension will analyze study period-level outcomes.

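### The ordinal retention model adjusts for a visit count that is either the same for everyone or, if clinic appointments are meant, a post-randomisation component of the outcome

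*Protocol article*

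**What the plan says.** The Analysis plan fits an ordinal logistic model to the three-level retention outcome and reports "odds ratios between arms, adjusted for the stratification factor and number of scheduled study visits". If proportional odds fails, each threshold gets its own logistic model. No version without the visit count is described.

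The term *study visits* has a settled meaning elsewhere. Under Study settings, "baseline, 6, and 12-month study visits take place at a clinical research site in the community". Under Follow-up of study participants, "Both intervention and control arm participants are asked to complete 6 and 12 month study visits".

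The outcome is built from other visits, those to the clinic. Under Key secondary outcomes, the top level is "Attended all scheduled primary care appointments in both 6-month study periods" and the bottom level is "Attended no scheduled clinic appointments in at least one 6-month study period". Clinic appointments differ in number between people: under SMS interactions with participants, "some participants may only have primary care appointments scheduled every three to four months". They can also change during follow-up, since every reminder says "Please call XXX-XXX-XXXX to cancel or reschedule".

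The virologic suppression model and the visit adherence model are adjusted for the stratification factor and account for within-participant correlation. Neither includes a visit count.

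**The concern.** The key secondary objective asks whether the intervention improves retention at 12 months, and the plan commits to intention to treat. An odds ratio that answers this should condition only on quantities fixed at randomisation.

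The number of primary care appointments scheduled during the trial year is not such a quantity. It accumulates over the same 12 months as the outcome and defines what *all kept* means. It could also respond to an intervention whose purpose is engagement with care. If the texts keep some people in care and those people therefore get more appointments, holding the count fixed removes that part of the effect. If unmeasured engagement drives both booking and attendance, conditioning on the count can also introduce an arm difference of its own. Either way, the reported odds ratio would not be the effect that the objective asks for.

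**Working it through.** **1. Literal reading.** Inputs: two follow-up study visits per participant, at 6 and 12 months, in both arms (Follow-up of study participants). By design the covariate equals 2 for everyone. With columns (constant, arm, count), count = 2 × constant, so the matrix has rank 2 out of 3 columns. In the ordinal model the thresholds play the role of the constant. The coefficient of the count cannot be estimated separately, and the arm odds ratio is the same with or without it. Counting the baseline visit (3 instead of 2) changes nothing.

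**2. Clinic-appointment reading.** The plan gives no figure for this model to reproduce and does not say how appointments are booked. All parameters below are therefore assumptions. Each scenario generates scheduled and kept appointments in two 6-month periods and derives the three levels. It then fits the proportional-odds model with arm and stratum, without and with the total number scheduled.

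*Slot model:* six two-monthly slots, with a chance of leaving care after each. The runs used 20,000 to 40,000 simulated participants. Ranges reflect different codings of the same scenario, for example how a period with nothing booked is classed.

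| Assumed route of effect | OR without count | OR with count |
|---|---|---|
| None (null) | 0.99–1.01 | 0.99–1.01 |
| Leaving care only, 15% v 8% per slot, keeping 70% in both arms | 1.70–1.88 | 0.91–0.98 |
| Leaving care only, smaller gap (15% v 12%) | 1.30 | 0.99 |
| Both: leaving 15% v 10%, keeping 65% v 75% | 1.96–2.06 | 1.62–1.92 |
| Both, a run in which the OR rose | 1.94 | 2.13 |
| Keeping only | 1.32–1.34 | 1.86–2.04 |

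The 15% v 8% scenario is strong. By the sixth slot, 1 − 0.85⁵ = 55.6% of controls and 1 − 0.92⁵ = 34.1% of the intervention arm have left, a gap of 21.5 points. With 15% v 12% the figures are 55.6% and 1 − 0.88⁵ = 47.2%, a gap of 8.4 points. The odds ratio is removed in both.

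*Other booking rules* (40,000 per scenario; log-odds of keeping 0.6 + 0.8 × unmeasured engagement, plus 0.4 for the intervention where keeping is affected):

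| Assumed booking rule | OR without count | OR with count |
|---|---|---|
| Number scheduled unrelated to arm | 1.57 | 1.58 |
| Missed visits rebooked with probability 0.8 | 1.65 | 1.25 |
| Next visit booked with probability 0.9 after a kept visit, 0.3 after a missed one | 1.50 | 1.35 |
| Intervention raises bookings only, keeping unaffected | 1.11 | 1.02 |
| Arm and unmeasured engagement both raise bookings, keeping unaffected by arm | 1.61 | 0.83 |
| As the row above, with a small benefit on keeping (0.1) | 1.70 | 0.89 |

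**3. The two thresholds.** In the bookings-only scenario, mean scheduled visits are 5.00 in controls and 6.25 in the intervention arm. The odds ratio for *some kept* goes from 1.49 to 1.02 on adjustment and that for *all kept* from 0.72 to 1.02. More appointments make the lower threshold easier to pass and the upper one harder. A single coefficient for the count cannot represent both, which strains the proportional-odds assumption.

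**The case against.** The strongest objection is that only one of the two readings does harm, and it is inferred. Taken at its word, the plan contains a redundant term and the arm odds ratio is unaffected. This stands: on the literal reading the point is one of wording.

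Second, the documents do not show that the intervention affects scheduling. Both arms get the same appointment reminders, so the invitation to cancel or reschedule does not by itself separate them, and booking practice is not described. A reader might infer that the covariate certainly lies on the causal pathway, or that adjustment will reverse the treatment effect. The documents support neither. The count *could* be affected. The clearer reversals (0.83 and 0.89) need the added assumption that unmeasured engagement drives both booking and attendance. In the slot model the adjusted value of 0.91–0.98 is close to no effect, and in some scenarios adjustment raises the odds ratio.

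Third, there is a plausible motive. Keeping every appointment is harder when there are more of them, so an unadjusted model can penalise an arm that books more care; the 0.72 above illustrates this. This stands as a limitation of the top outcome level. It does not justify conditioning on a post-randomisation count in the main comparison. The visit adherence rate, the other key secondary outcome, already handles the number of appointments through its denominator, "excluding cancelled or rescheduled visits".

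**Conclusion.** The point holds in limited form. The covariate either adjusts for nothing or, if clinic appointments are meant, changes what is estimated, so that the odds ratio is no longer the total intention-to-treat effect on retention. That second conclusion follows from the timing of the count and the definition of the outcome, and needs no simulation.

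The size and direction of the distortion do rest on assumed booking rules. They range from no change (the null, or 1.57 v 1.58 with scheduling unrelated to arm), through attenuation, to removal (about 1.3–1.9 down to about 1.0 when the effect runs only through staying in care). They extend to inflation (1.32–1.34 up to 1.86–2.04 when it runs only through visit-keeping). Reversal is possible only under further assumptions and should not be taken as expected.

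The point touches one of two key secondary retention outcomes. The primary virologic analysis, the visit adherence model and the sample size are not affected. It should be corrected before analysis.

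**What to change.** Delete the visit count from the main ordinal model and from the fallback threshold-specific logistic models, leaving arm and the stratification factor. If adjustment for visit intensity is wanted, use a baseline quantity: entry route (new to clinic v poorly retained), or appointments scheduled in the 12 months before enrolment. Visit history is already checked in the EMR at screening. If a model with the number of primary care appointments scheduled during follow-up is kept, say which visits are counted and label it exploratory.

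The cost is one line of wording and no new data collection. The small downside is that participants with more appointments find the *all kept* level harder to reach in the unadjusted model. Reporting the threshold-specific results and the visit adherence rate alongside makes this visible.

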### Additional analyses

#### Cost and cost-effectiveness evaluation

In an era of limited health care resources, a key focus of intervention evaluation is whether the intervention is resource-efficient, thus we plan to investigate the societal economic value of the SMS intervention as well as the economic effect of SMS on the current system of care. Our economic evaluations will test whether the cost of the SMS platform minus any associated savings in downstream costs results in outcomes that are worth this cost. We will conduct two main analyses using welfarist and extra-welfarist approaches: 1) a cost-effective analysis (CEA) of the SMS intervention compared with SMS reminders alone, and; 2) a cost-benefit analysis (CBA) of the intervention with a return on investment (ROI) analysis to the clinic implementing the intervention [46].

CEA determines how to maximize health care effects given the resources available or the health benefit per dollar spent. We will report the incremental cost-effectiveness ratio (ICER) for the SMS intervention compared with SMS appointment reminders alone. Our main outcome will be cost/quality-adjusted life years (QALYs), estimating survival based on patients’ viral load. However, we will also look at differences in cost per differences in meaningful change in virologic suppression. We will use EMR, laboratory, and patient-reported health care utilization data, as well as interviews with the developers and implementers of the SMS intervention and national cost estimates to determine costs. A discount rate of 3% will account for time preference. One-way and probabilistic sensitivity analyses using Monte Carlo simulations will determine the effect of different assumptions on the outcomes of the analysis [47],[48].

Our second economic analysis will be a CBA, which will allow us to determine the economic value of the SMS intervention and SMS appointment reminders alone to the health care system. Cost-benefit analysis determines the intervention with the highest net benefit. Net benefit results can also be ranked for decision-making purposes within a fixed budget [48]. Willingness to pay (WTP) questions will measure benefit. In addition, we will measure the costs of the intervention, any increased or savings in health care expenditures resulting from the intervention and calculate the return on investment of the health care system… This analysis will use the perspective of the health care system and allow intersectoral costs and effects, including non-health related costs.

#### Qualitative sub-study

In order to better understand the experience of the intervention, we will recruit participants for a qualitative sub-study as they finish the 12-month intervention period. We will use one-on-one semi-structured interviews to assess satisfaction with and perceived benefits of the text messages and explore issues related to: 1) barriers to and facilitators of responding to intervention text messages, including access to and comfort with text messaging; 2) frequency and content of text messages, and; 3) privacy and confidentiality. We will also explore the acceptability of other technologies for future interventions.

#### Ancillary studies

We will perform a descriptive analysis of text message communication, including rates of response and reasons for non-response, rates of self-reported cell phone service interruption and reasons for service interruptions, and satisfaction with the amount and content of text messages.

#### Potential harms and human subjects protection

The study was approved by the Committee on Human Research (CHR) at the University of California San Francisco and it has also received a Certificate of Confidentiality from the National Institutes of Health. The greatest potential harm to the study is inadvertent disclosure of HIV status through text messages. However, none of the text messages includes the words HIV or AIDS. Another potential harm is the inconvenience caused by technical glitches, including receipt of messages at an unexpected time, missed messages, or too many messages. There is a possibility that participants may exceed the limit of their text messaging plan and have to pay extra for messages related to the study. Other potential harms include feeling uncomfortable or sad during questionnaire administration or discomfort with phlebotomy. Research assistants receive training to address such risks and carefully review them with participants. Participants are invited to able to ask questions before, during, and following the informed consent process. Adverse events are reported to the study principal investigators and the UCSF CHR using standard protocols.

## Discussion

This study protocol describes a randomized controlled trial designed to improve retention in care and virologic suppression among patients in a U.S. safety-net HIV clinic through an informational, motivational, and supportive text messaging intervention. There are several unique features of the trial that are worth highlighting. First, we sought to develop a text message intervention that could easily be replicated and deployed in a clinic setting without requiring additional staffing, as opposed to other SMS interventions that require in-person follow up of text communication. Second, to increase generalizability, the intervention is clinic-wide, rather than focused on a specific demographic or risk factor sub-group. As such, one of the challenges in designing the intervention was creating text messages that appealed to the clinic population at large. For example, in our formative focus groups, participants who used illicit substances wanted messages about substance use while those who did not use substances or who had been sober for long periods of time did not want any substance use messages. A similar phenomenon was observed with regard to spiritual and religious content. This finding helped us focus the content domains. A third unique feature of the study is that it does not provide cell phones or airtime. While this aspect of the study also increases its generalizability, we acknowledge that cell phone service interruption is common and can reduce intervention exposure. Accordingly, we will supplement the primary intent to treat analysis with per protocol analyses that adjust for intervention exposure. These trial features enable the opportunity to study intervention delivery, as well as associated barriers and costs, in a “real world” context.

One of the key elements in the success of any text messaging trial is partnering with a vendor who can accommodate control and intervention assignments, immediately troubleshoot technical glitches, and securely manage the relationship between phone numbers and de-identified study IDs. The use of pilot participants to test our text messaging protocols allowed us to realize early on that our first vendor did not have the capacity to execute the study as envisioned and to contract with a new vendor.

With regard to study recruitment, it is worth noting that the eligibility criterion of a detectable HIV viral load within 28 days of screening constitutes a rigorous definition of viremia, but that it frequently requires phlebotomy to determine eligibility, posing a potential challenge to recruitment. In addition, recruitment happens in the clinic while enrollment occurs at a geographically distinct research site. Though research assistants offer facilitators such as bus tokens and same-day baseline appointments, inevitably some potential participants fail to present to the research site, even despite reminders. However, we believe that a real strength of our trial lies in this geographic separation, in that it minimizes the possibility that attending study visits will affect the study outcome of clinic appointment attendance.

In sum, we anticipate that findings from our study will provide valuable information about the use of theory-based text messaging to promote retention in HIV care and virologic suppression, further elucidate the challenges of using texting technology with marginalized urban populations, and help inform the development of new mobile health strategies to improve HIV care cascade outcomes.

## Authors’ original submitted files for images

Below are the links to the authors’ original submitted files for images. Authors’ original file for figure 1 Authors’ original file for figure 2
